### Outcomes {12}

The primary outcome is a change from baseline of moderate and vigorous physical activity in minutes or steps per week. Therefore, moderate and vigorous physical activity levels are aggregated and measured by one continuous variable. Physical activity is measured continuously with the tracker-based device, and algorithms are implemented to calculate amounts of different intensities [41]. Intensity levels are defined in accordance to intensity classification of Freedson et al. [48].

In addition, physical activity is assessed with questionnaires at four time points (*t*_0_, *t*_1_, *t*_2_, and *t*_3_).

As the analysis of the patient-relevant outcomes morbidity, mortality, and comorbidity of diabetes patients requires long-term studies, which are not feasible in this study due to limited project resources, the clinical outcomes HbA_1c_, body weight, and blood pressure are used as relevant surrogate parameters for these outcomes [13]. Therefore, secondary endpoints are medical parameters (HbA_1c_, TIR (time in range), BMI, and blood pressure). As covariates, psychosocial parameters (generic or diabetes-specific: health-related life satisfaction, self-efficacy, motives, volition, stages of behavioral change, personality, intention, and self-concordance), socio-demographic variables (age, gender, family background, family status, and socio-economic status), physical and mental health, comorbidities, alcohol as well as tobacco consumption, nutritional awareness, usage behavior and user satisfaction (with regard to the activity tracker and smartphone app), diabetes disease and treatment (e.g., medication), participation in external interventions, and severity of the disease are considered. The medical parameters of the healthy individuals are measured at four time points and those of the diabetes patients are collected via routine visits at the cooperating diabetes center. The data about covariates are captured with questionnaires at the same four time points. The items of the questionnaires originate from validated instruments.

In general, changes in the arithmetic means and variances of these mentioned outcomes from baseline are analyzed and compared between the intervention and control groups as well as between the four time points.

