### Sample size {14}

The sample size was calculated according to the primary hypothesis. The correlation between the results of the different measurement times is estimated to be 0.33 based on similar studies [66]. Regarding the effect size, the results of similar studies show that a medium effect can be assumed, which is why the effect size is estimated at *d*=0.5 and *f*^2^=0.15 [27, 28, 33, 66]. A dropout rate of 15% is derived from one of these studies [66]. For a power (1-β) of 0.8 with a significance level of *α*=0.05, assuming an effect size of *f*^2^=0.15, an adjustment with design effect, and a drop-out rate of 15%, a sample size of at least 1642 participants is necessary. With the help of the results of the pre-studies, a more precise calculation of the sample size is possible and the sample size can be adjusted if necessary.

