Since comparisons between participants in the intervention and control groups as well as comparisons of participants at different time points take place, a linear mixed model with two levels will be calculated to test the primary hypotheses [78]. The dependent variable is moderate and vigorous physical activity per week measured with a questionnaire. In the linear mixed model, time (*t*_0_ to *t*_3_) is the intra-class factor, and grouping (intervention group with tracker-based device, intervention group with tracker-based device and digital behavior intervention, and control group) is the inter-class factor [78]. The covariates psychosocial factors, socio-demographic factors, physical and mental health, comorbidities, alcohol and tobacco consumption, nutritional awareness, usage behavior and user satisfaction (with regard to the activity tracker and app), diabetes disease and treatment, participation in external interventions, and severity of the disease are assessed as categorical variables. Random intercepts are assumed while all other effects are regarded as fixed. The null model will be calculated and compared with alternative models regarding its fit via Akaike and Bayesian information criterion [78, 79]. Further, interactions will be considered and will be included in the model if the explanatory power of the model is strengthened. The same analysis will be performed for the assessment of secondary endpoints. Effects of all analyses will be considered significant if *p* < 0.05. All assumptions of the statistical tests will be checked in advance graphically and by appropriate tests. Bonferroni correction will be applied to counteract the problem of multiple testing [80].

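### The primary mixed model has only a random intercept and names no safeguard, so standard errors for change from baseline at individual visits are right only if variances and correlations are constant over nine months

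*Protocol article*

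**What the plan says.** Section {20a} of the protocol article tests the primary hypotheses with a two-level linear mixed model. On the outcome it says "The dependent variable is moderate and vigorous physical activity per week measured with a questionnaire", and on the within-person factor "time (*t*_0_ to *t*_3_) is the intra-class factor". Three groups form the between-person factor. The random part is given as "Random intercepts are assumed while all other effects are regarded as fixed". For the other outcomes, "The same analysis will be performed for the assessment of secondary endpoints".

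The section names no random slope, residual covariance structure, visit-specific variance or robust standard error. It does promise to compare a null model with alternative models by AIC and BIC, to check assumptions, and to apply a Bonferroni correction.

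The Sample size section {14} plans with one value: "The correlation between the results of the different measurement times is estimated to be 0.33 based on similar studies". The Outcomes section {12} defines the primary outcome as a change from baseline and adds that "changes in the arithmetic means and variances of these mentioned outcomes from baseline are analyzed and compared".

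**The concern.** A random intercept with independent residuals is compound symmetry: the spread is the same at baseline, 3, 6 and 9 months, and two measurements 9 months apart are as strongly correlated as two taken 3 months apart. The fitted model therefore pools all within-person variation into one quantity and gives the 3-, 6- and 9-month changes the same standard error. If the true pattern differs by visit, some of these standard errors are too small and others too large.

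This matters because the primary outcome is a change from baseline and the research questions ask about sustainable improvement, on which the 9-month change bears most directly. The same structure is carried over to HbA1c, BMI and blood pressure. Nothing in the section says what happens if it does not fit.

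**Working it through.** **No figure of the plan to reproduce.** The protocol states no standard error and no SD by visit. Its total of 1642 enters only as a sample size and cancels from every ratio below.

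**Inputs**
- Average correlation r̄ = 0.33 (Sample size {14}).
- 1642 × 0.85 / 2 ≈ 698 per arm, with the two intervention groups pooled (1:1 allocation and 15% dropout from the protocol).
- Assumed: SD 1 at every visit unless stated, balanced data, two-sided 5%.
- Assumed: the correlation at each lag. The documents give none.

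**Formulas** (visits 0 to 3; V is the true covariance matrix)
- Variance the random-intercept model assigns to any change: 2 × (mean variance − mean covariance). With equal SDs this is 2(1 − r̄) = 2 × 0.67 = 1.34.
- True variance of the change from baseline at visit t: V₀₀ + V_tt − 2V₀t. With equal SDs this is 2(1 − r_lag).
- SE ratio (model/true) = √(model variance / true variance).
- Actual type I error = 2 × [1 − Φ(1.96 × ratio)].

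**If the planning value holds as written.** With 0.33 for every pair, the ratio is √(0.67/0.67) = 1 at each visit. The model SE is √(1.34 × 2/698) = 0.062, which is correct, and the error rate is 5%.

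**If correlations fall with time.** Each pattern averages 0.33 over the six pairs; for example (3×0.36 + 2×0.31 + 0.28)/6 = 1.98/6 = 0.33.

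| Assumed r at 3/6/9 months | SE ratio, 3-month change | Type I | SE ratio, 9-month change | Type I |
|---|---|---|---|---|
| 0.36/0.31/0.28 (nearly flat) | √(0.67/0.64) = 1.02 | 4.5% | √(0.67/0.72) = 0.96 | 5.9% |
| 0.40/0.30/0.18 (milder fall) | √(0.67/0.60) = 1.06 | 3.8% | √(0.67/0.82) = 0.90 | 7.6% |
| 0.474/0.225/0.107 (AR(1)) | √(0.67/0.526) = 1.13 | 2.7% | √(0.67/0.893) = 0.87 | 9.0% |

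In the AR(1) case the 6-month ratio is √(0.67/0.775) = 0.93, with type I error 6.8%. A simulation of that case (5000 runs, 200 per arm) gave 2.7%, 6.4% and 8.6% at 3, 6 and 9 months.

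**If variances differ but correlation stays at 0.33**
- SDs 1, 1, 1, 1.2: model variance 2 × (1.11 − 0.363) = 1.494; true 9-month variance 1 + 1.44 − 0.66×1.2 = 1.648; ratio 0.95; type I error 6.2%.
- SDs 1, 1.2, 1.1, 1.0: model variance 2 × (1.1625 − 0.3806) = 1.564. At 9 months the true variance is 1.34, ratio 1.08, type I error 3.4%. At 3 months the true variance is 1.648, ratio 0.97, type I error 5.6%. The direction is reversed.
- SDs falling 1.2, 1.1, 1.0, 0.9: ratios 0.92, 0.96 and 0.99 at 3, 6 and 9 months. Here the 3-month SE is the one too small.

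**Joint group-by-time test.** Under the model its statistic is a weighted sum of chi-squares, with weights equal to the non-zero eigenvalues of the centred correlation matrix divided by 0.67. In the AR(1) case these are 0.60, 0.88 and 1.52, which average 1, so the errors largely cancel. For three groups (6 df), type I error is 5.9% for AR(1), 5.3% for the milder fall and about 5% for the nearly flat pattern.

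**Bonferroni.** If the correction covers three visit contrasts (an assumption), the nominal level is 1.67%, with critical value 2.394. In the AR(1) case the actual level at 9 months is 2 × [1 − Φ(2.394 × 0.866)] = 3.8%. The relative inflation remains, but the rate is below 5%.

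**The case against.** The strongest objection is that the documents contain no evidence of the pattern that does the damage. Their one figure, a common correlation of 0.33, agrees with compound symmetry, and a falling correlation is brought in from outside. This stands, and it limits the point to a conditional one.

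A reader might infer that the 9-month standard error will be too small and its type I error above 5%. The documents do not support that: the direction depends on an assumed decay or rise in variance, and other patterns reverse it.

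A reader might also infer from the sentence on means and variances in Outcomes {12} that the plan contradicts itself. It does not. Planning to compare variances is not expecting them to differ, and the sentence says nothing about correlations.

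Nor is the 9-month arm difference named as the single primary contrast. The joint test is barely affected, and with equal variances the comparison of groups at a single visit is not distorted even under AR(1).

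It can also be said that residual covariance is detail for an analysis plan, that a random intercept can be combined with a structured residual, and that AIC/BIC comparison and assumption checks are promised. This stands only in part. The article does choose the random part itself; the alternative models are not described as covariance alternatives, and no fallback follows a failed check.

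**Conclusion.** The point holds conditionally. On its usual reading, the stated model is restrictive and unprotected: standard errors of visit-specific changes from baseline depend on constant variance and constant correlation across the four visits. If those hold, nothing is wrong. If correlations fall with time while averaging 0.33 and variances stay equal, the 9-month standard error is about 4% to 13% too small and the 3-month one about 2% to 13% too large. The matching unadjusted error rates are 5.9% to 9.0% and 4.5% to 2.7%. Under other variance patterns the errors go the other way. All these figures rest on assumed patterns and complete, balanced data. The change is worth making because it is cheap and removes the dependence, not because the documents show that the present model will fail.

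**What to change.** Replace the random-intercept sentence in section {20a} with: visit enters as a categorical factor, and the four repeated measurements have an unstructured 4×4 covariance matrix. Robust (sandwich) standard errors may be added against unequal variances between arms. Use the same structure for the secondary endpoints, and keep the random-intercept fit as a sensitivity analysis.

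The cost is wording and code. The model estimates 4 variances and 6 covariances, 10 parameters instead of 2, which is negligible with about 1642 × 0.85 ≈ 1396 participants remaining. Compound symmetry is a special case of the unstructured matrix, so almost nothing is lost if the flat 0.33 is right.

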### Trial design {8}

The monocentric, pragmatic RCT has a parallel group design with an allocation ratio of 1:1. Tests of equivalence will be performed to compare the intervention group wearing a smartwatch with an activity tracker in everyday life with the control group that does not wear the device. Furthermore, 50% of the participants in the intervention group will also receive a digital motivational intervention via a smartphone app. The planning and implementation of the study is orientated towards the Declaration of Helsinki [37].

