### Participant timeline {13}

Participants who give their informed consent and fulfill the inclusion criteria are assessed at four timepoints (see Table 1 and Fig. 1). At baseline, a questionnaire with socio-demographic questions [51] is administered, and at all four time points, a questionnaire with health-related questions [52], questions regarding physical activity [53, 54], a psychosocial questionnaire [55–64], and questions regarding the use of tracker-based devices and apps outside this study is administered. In addition, the diabetes parameters are measured in a standardized way by qualified study personnel at all four time points. Questions regarding the usability of and satisfaction with the app and the tracker-based device [65] are asked after 6 months and regarding the follow-up use of the device after 9 months.

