### Methods in analysis to handle protocol non-adherence and any statistical methods to handle missing data {20c}

The collected data will be analyzed in terms of the intention-to-treat (ITT) method, which means that data from all subjects will be assessed because they more realistically reflect the everyday life of the participants [81]. Following the ITT evaluations, the analyses will be carried out again with the per-protocol collective and compared with the results according to ITT using sensitivity analyses [82]. The reasons for withdrawal and drop-out from the trial will be assessed for all groups, and the characteristics of these subjects will be compared between the intervention and control groups. Data will be included in the analyses up to the point of drop-out. The physical activity data measured with activity tracker will be preprocessed using the R package “accelerometry” [83]. Missing and unreliable values will be replaced by the average of neighboring data [83]. For all data, missing values will be quantified and checked if they are not missing at random.

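### Choosing the primary mixed model by AIC/BIC over questionnaire covariates, with no stated rule for covariate gaps, can reward incompleteness; one listed covariate, user satisfaction, cannot exist for controls

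*Protocol article*

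**What the plan says.** Section {20a} tests the primary hypotheses with a two-level random-intercept model. "The dependent variable is moderate and vigorous physical activity per week measured with a questionnaire". Time (t0 to t3) and the three-way grouping are the main factors. About a dozen covariate domains follow, all treated as categorical, among them "usage behavior and user satisfaction (with regard to the activity tracker and app". Model choice is by information criteria: "The null model will be calculated and compared with alternative models regarding its fit via Akaike and Bayesian information criterion". Interactions enter if they add explanatory power, and the secondary endpoints are analysed in the same way.

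On the covariates, Outcomes {12} says "The data about covariates are captured with questionnaires at the same four time points". Participant timeline {13} is more specific for one of them: "Questions regarding the usability of and satisfaction with the app and the tracker-based device [65] are asked after 6 months". Trial design {8} describes "the control group that does not wear the device".

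On missing data, section {20c} adopts intention-to-treat, "which means that data from all subjects will be assessed". Its one filling rule, "Missing and unreliable values will be replaced by the average of neighboring data", comes directly after the sentence on preprocessing tracker data and carries the same citation. For data in general, missing values are to be counted and their mechanism examined; no handling is given.

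**The concern.** AIC and BIC rank models only when every model is fitted to the same observations. With the outcome in minutes per week, each row removed lowers −2 log-likelihood whether or not the covariate explains anything. A covariate with gaps can therefore win because it has gaps.

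The comparison shapes the model that gives the primary arm effect. Two things are at stake. The model could be selected by missingness rather than fit. The effect could then be estimated on the rows of people who answered everything, with less precision and possible selection, although the plan promises data from all subjects.

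**Working it through.** No planning figure is in dispute; 1642 participants, the 1:1 allocation, four visits and the correlation of 0.33 between visits serve only as inputs.

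**1. A covariate incomplete by design (no assumed rate)**
- Planned participant-visits: 1642 × 4 = 6568.
- Tracker wearers at 1:1: 1642 / 2 = 821. Controls: 821, with no device to rate.
- Satisfaction asked after 6 months gives at most 821 × 1 = 821 observable rows, and 821 / 6568 = 12.5%.
- A fit on those rows has no control arm, a single visit and one row per person. Neither the control contrast, nor the time effect, nor the random intercept can be estimated.
- If the 6-month answer is copied to all of a wearer's visits, or if the general statement in {12} about four time points is taken literally, the maximum is 821 × 4 = 3284 rows (50%). Controls still contribute none.

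**2. What unequal rows do to AIC and BIC**

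Under a random-intercept model with correlation ρ, removing one of a participant's four rows lowers −2 log-likelihood on average by

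ln(2πσ²) + 1 + ln[(1 − ρ)(1 + 3ρ)/(1 + 2ρ)].

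With ρ = 0.33 and σ = 1: 2.838 + ln(0.67 × 1.99 / 1.66) = 2.838 − 0.219 = 2.62 per row. With an assumed SD of 150 minutes, add 2 ln 150 = 10.02, giving 12.64 per row.

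This was checked by simulation: 1642 × 4 rows, σ = 1, ρ = 0.33, arms 50/25/25, one pure-noise three-level covariate missing completely at random, maximum likelihood, four runs per rate. Negative values favour the covariate.

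| Missing | Rows lost (mean) | 2.62 × rows lost | AIC change, different rows | BIC change, different rows | AIC change, same rows | BIC change, same rows |
|---|---|---|---|---|---|---|
| 1% | 62.8 | 164 | −165 | −151 | −0.1 | +13.5 |
| 5% | 317.2 | 831 | −846 | −833 | +0.4 | +13.9 |
| 10% | 655.2 | 1716 | −1725 | −1713 | +0.7 | +14.1 |

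The penalty for two extra parameters is 4 (AIC) or 2 × ln 6568 = 17.6 (BIC), far too small to offset the artefact at any of these rates. On different rows AIC preferred the useless covariate in every run. In minutes at SD 150, the 1% case would be about 12.64 × 62.8 = 794.

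**3. Item non-response (illustrative only)**

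If each of k covariates is missing on a share m of rows, independently, the complete-row share is (1 − m)^k.

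| k | m = 1% | m = 2% | m = 5% |
|---|---|---|---|
| 10 | 90% | 82% | 60% |
| 20 | 82% | 67% | 36% |

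The protocol gives neither m nor k. If the gaps fall in the same respondents, the loss approaches m itself: 2% rather than 33% for k = 20 at m = 2%.

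**The case against.** The strongest reply is that the protocol never says incomplete rows are dropped. The AIC/BIC rule is sound on common rows, and a condensed article may leave item non-response to an analysis plan that is not shown. That stands: a reader might infer that the models will be fitted to different rows, but this is the software default and not a statement in the document.

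A reader might also infer that the intention-to-treat model must lose participants. The document does not support this either. A gap at one visit removes a row; a participant is lost only if a once-measured covariate, such as baseline socio-demographics, is missing or every row is incomplete. Section {20c} already accepts partial contribution up to drop-out.

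The retention figures should not be read as forecasts. Outcome and most covariates share the same online questionnaires, so a skipped questionnaire removes the row from the null model too and creates no artefact. Closed-ended electronic entry, reminders and phone contact should limit item gaps.

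Because the covariates are categorical, a missing or not-applicable level would fit the plan. For ordinary gaps that is a good answer. For satisfaction, the level would contain all controls. With the answer attached to each wearer it would coincide with the control arm, so the arm contrast could not be separated from it.

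One sentence in {11c} has control participants instructed to wear the device. It conflicts with {8}, with the intervention description and with the Discussion, and is not relied on here.

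What survives is the satisfaction covariate. Its incompleteness follows from the design, so it is not merely a detail left to another document.

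**Conclusion.** The concern holds in a conditional form, plus one part that is not conditional.

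- **Unconditional:** a listed covariate has no value for any of the roughly 821 controls and, on the stated schedule, is observable in at most about 821 of 6568 participant-visits. A between-arm model containing it as observed cannot use all subjects.
- **Conditional on available-row fitting:** the AIC/BIC comparison is invalid and favours incomplete covariates. The artefact was about 165 AIC points at 1% missing with outcome SD 1, and is larger in minutes.
- **Unknown in size:** further loss from item non-response. The 1–5% rates and their independence are assumptions.

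The plan should be changed, because the selection rule governs the primary effect and is carried over to every secondary endpoint. It would go too far to say that the protocol prescribes complete-case fitting or that participants will necessarily be lost.

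**What to change.** In {20a} and {20c}, state that:

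1. The primary arm effect comes from one prespecified intention-to-treat mixed model with arm, time, arm-by-time, disease stratum and a named set of baseline covariates. Baseline activity is already in the model as the t0 response.
2. Gaps in baseline covariates are filled by a simple rule blind to arm (overall mean, or a missing category), so that no randomised participant with an outcome is dropped for a covariate.
3. Device-use and satisfaction covariates are kept out of the between-arm model. They can be studied descriptively within the tracker arms.
4. Any AIC/BIC comparison is secondary and made on one common set of rows.

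The cost is a few sentences and a slightly less flexible primary model. No new data are needed, and the same model form can serve the secondary endpoints.

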### Objectives {7}

In this trial, it is hypothesized that the moderate and vigorous physical activity of the participants in the groups (no diabetes, diabetes and pre-diabetes) with activity tracker increases statistically significantly in terms of the target values at the 5% level of significance over time (at baseline (*t*_0_), after 3 months (*t*_1_), after 6 months (*t*_2_) and after 9 months follow-up (*t*_3_)). The measurements of moderate and vigorous physical activity with questionnaire are hypothesized to be statistically significantly different at the 5% level of significance from the measurements of physical activity with the activity tracker. In addition, an explorative hypothesis is tested: The moderate and vigorous physical activity in minutes per week measured with the activity tracker of participants in the different intervention groups (tracker-based intervention alone or tracker-based intervention combined with digital motivational intervention) increases differently over time.

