## Trial status

This is protocol version number 7 14 June 2022. The recruitment is delayed to minimize the risk of a SARS-CoV-2 infection and started in January 2022; the last patient will be enrolled in December 2022. The first results of this study are expected in 2023.

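### The primary hypothesis names no control comparison, and the group-by-time term that compares change between arms enters the model only if it improves the model

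*Protocol article*

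**What the plan says.** Objectives {7} states the main hypothesis for "participants in the groups (no diabetes, diabetes and pre-diabetes) with activity tracker": their moderate and vigorous physical activity (MVPA) "increases statistically significantly in terms of the target values at the 5% level of significance over time". Control is not mentioned. The only hypothesis there about activity changing differently between arms is labelled explorative, and it sets the two tracker arms against each other.

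Outcomes {12} defines the endpoint: "The primary outcome is a change from baseline of moderate and vigorous physical activity in minutes or steps per week". It adds, in general terms, that changes are compared between intervention and control and between time points.

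Statistical methods for primary and secondary outcomes {20a} tests the primary hypotheses with a two-level linear mixed model of questionnaire MVPA. Time (t0 to t3) and a three-level group (tracker, tracker plus digital intervention, control) are the named factors, with random intercepts and all other effects fixed. On model choice it says: "The null model will be calculated and compared with alternative models regarding its fit via Akaike and Bayesian information criterion". Next, as a separate step, "interactions will be considered and will be included in the model if the explanatory power of the model is strengthened". Group-by-time is not singled out.

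**The concern.** Two statements combine badly. First, a hypothesis of increase within the tracker arms can be met by anything that raises reported activity in everyone: regression to the mean, repeated questionnaires, season, or changing pandemic conditions. The control arm exists to remove such influences, and the hypothesis as worded does not use it.

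Second, when baseline is one of the modelled outcomes, a difference between arms in change from baseline is the group-by-time interaction. The time main effect pools control with intervention. The group main effect averages the untreated baseline with the three later visits. The term that answers the trial's question is thus optional and decided by the data, while the terms that are always present answer it only indirectly or not at all.

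**Working it through.** **Inputs.** From Sample size {14}: 1642 participants, 15% dropout, correlation 0.33 between visits, planning effect d=0.5, α=0.05 (taken as two-sided). From Trial design {8}: 1:1 allocation, with half of the intervention arm also receiving the digital intervention. From Background {6a}: SMDs for MVPA of 0.17 (wearable alone) and 0.28 (wearable with behavioural intervention), both from the same meta-analysis. Assumed here: compound symmetry, complete data on those analysed, and a constant effect at t1–t3. The protocol gives no figure of its own on this point to reproduce; 1642 is taken as stated.

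Analysed: 1642 × 0.85 ≈ 1396, split 698 control / 349 tracker / 349 tracker plus digital, so 698 wearers.

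**1. Shared drift and the within-arm hypothesis.** For one pre–post contrast among wearers, SE = √(2 × (1 − 0.33)/698) = 0.0438 SD. Drift above 1.96 × 0.0438 = 0.086 SD is significant. The chance of declaring an increase with no intervention effect is Φ(drift/SE − z):

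| Assumed drift | z = 1.960 (unadjusted) | z = 2.394 (Bonferroni, three contrasts) |
|---|---|---|
| 0.10 SD | 63% | 46% |
| 0.15 SD | 93% | 85% |

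**2. The group-by-time test.** Three groups by four times gives (3 − 1)(4 − 1) = 6 df. For SMDs 0.17/0.28 the weighted mean effect is (349 × 0.17 + 349 × 0.28)/1396 = 0.1125, and

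S = 698 × 0.1125² + 349 × 0.0575² + 349 × 0.1675² = 19.78.

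The pattern 0,1,1,1 over time has a centred sum of squares of 0.75, so the noncentrality is 19.78 × 0.75/0.67 = 22.1. The 5% critical value is 12.59, and power is 96%.

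**3. If a fit criterion decides inclusion.** AIC keeps the term if the likelihood-ratio statistic exceeds 2 × 6 = 12 (p < 0.062). BIC needs 6 × ln(1396) = 43.4 counting participants, or 6 × ln(4 × 1396) = 51.8 counting observations (p about 1e-7 or 2e-9).

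| True SMDs (tracker / tracker plus digital) | Power of 5% test | AIC keeps | BIC keeps |
|---|---|---|---|
| 0.17 / 0.28 | 96% | 97% | 2.0–7.5% |
| 0.20 / 0.20 | 86% | 88% | 0.3–1.6% |
| 0.50 / 0.50 | >99.9% | >99.9% | >99.8% |

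**4. What is left if the term is dropped.** The group main effect averages four visits, one untreated, so a constant effect d appears as 0.75d. The variance of a four-visit mean is (1 + 3 × 0.33)/4 = 0.4975, so its noncentrality for 0.17/0.28 is 19.78 × 0.75²/0.4975 = 22.4 on 2 df, giving 99% power.

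**The case against.** The strongest reply is that the randomised comparison is still made. {20a} keeps the three-level group factor in the model unconditionally and justifies the model by comparisons between intervention and control; Outcomes {12} and Trial design {8} also state that comparison. Under no treatment effect the group main effect has expectation zero at every visit, so it is a valid test, and step 4 shows it is powerful. This stands. A reader might infer that the randomised comparison could go untested altogether, and the protocol does not support that. What is not guaranteed is the comparison of *change*, which is the stated outcome.

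The AIC/BIC gate on interactions is also an inference. {20a} names those criteria for null versus alternative models; the interaction sentence speaks only of explanatory power and gives no criterion. The 2–8% needs BIC alone to decide, and effects at the low end of those cited. The same background section cites 0.49 for MVPA with a behavioural intervention; at 0.17/0.49 BIC would keep the term in 85–95% of trials.

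The drift sizes are illustrations with no source in the protocol. Enrolment that "started in January 2022; the last patient will be enrolled in December 2022" spreads baselines over a year, so seasonal drift would partly average out.

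It is also tempting to say that selecting the term by fit invalidates its p-value. For the 6-df test under AIC this does not follow: the AIC threshold of 12 lies below the 5% critical value of 12.59, so the overall false-positive rate stays at 5%.

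Finally, a SAP may settle the exact contrast and time point. That is fair, but the comparator-free hypothesis and the conditional rule are stated here, and a SAP would have to depart from them.

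**Conclusion.** The point holds in this form: the primary hypothesis names no comparison with control, and the term that compares change from baseline between arms is included only conditionally. The first part means that a shared drift can confirm the hypothesis with no intervention effect (46–63% at an assumed 0.10 SD, 85–93% at 0.15 SD, for one pre–post contrast in about 698 wearers). The second means that the primary outcome may be compared between arms only through a main effect that shrinks a constant effect to three quarters and does not test difference in change.

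The risk of losing the interaction runs from negligible to severe. It is negligible at d=0.5 under either criterion, and small under AIC at 0.17/0.28. It is severe only if BIC alone governs at those smaller effects. These figures rest on the protocol's correlation and dropout, compound symmetry, and a constant effect from t1 to t3.

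**What to change.** In Objectives {7}, reword the primary hypothesis as a difference between intervention and control in the change in MVPA. In {20a}, always include group, time and group-by-time, and make the group-by-time contrast the primary test; pooled tracker arms versus control at t2 is one option. Limit fit-based selection to terms other than these treatment terms.

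The cost is wording only: no new data, visits or participants.
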